# The Effect of Electroacupuncture on Microcirculation in Patients With Hypertension and Cognitive Impairment: Protocol for a Multicenter Randomized Controlled Trial

**DOI:** 10.2196/70876

**Published:** 2025-10-21

**Keywords:** acupuncture, mild cognitive impairment, hypertension, microcirculation, randomized controlled trial

## Abstract

**Background:**

Hypertension is a significant risk factor for cardiovascular diseases and is associated with an increased risk of mild cognitive impairment (MCI). The lack of effective treatment for these conditions underscores the urgent need for novel therapeutic approaches. Previous studies have indicated that microcirculation serves as the pathological basis for the comorbidity of hypertension and cognitive dysfunction. Our initial clinical studies have indicated that acupuncture could be a safe and effective treatment for managing hypertension and MCI. Whether acupuncture can enhance hypertension and cognitive impairment by modulating microcirculation, and the precise mechanisms involved, warrants further exploration.

**Objective:**

The objective of the trial is to evaluate the clinical efficacy of electroacupuncture on MCI of patients with hypertension and to explore whether it can improve hypertension and cognitive impairment by regulating microcirculation.

**Methods:**

In this multicenter, large-scale, single-blind, randomized controlled trial, we will recruit 252 patients with hypertension and cognitive impairment from 3 hospitals and randomly assign them to 3 groups in a 1:1:1 ratio: the electroacupuncture group, the sham electroacupuncture (SEA) group, and the waiting list group. The electroacupuncture group and SEA group will receive either electroacupuncture or SEA for 12 weeks, while the waiting list group will not receive acupuncture treatment for the first 12 weeks. The primary outcome will be the changes in overall cognitive function, as measured by the Montreal Cognitive Assessment. The secondary outcomes include blood pressure status, subdomain cognitive function, mental status, sleep quality, hemodynamics, and microcirculation indicators.

**Results:**

The study protocol has been approved by the institutional review board of the First Affiliated Hospital of Tianjin University of traditional Chinese medicine. This study was registered on April 26, 2024, with the Chinese Clinical Trial Registry. Data collection began in May 2024 and ended in April 2025. Currently, data from this trial are in the collection phase, and no data analysis has been performed. As of January 1, 2025, we have collected data from 65 patients. The results of this trial are expected to be submitted for publication in July 2026.

**Conclusions:**

This clinical trial aims to compare the efficacy of electroacupuncture versus SEA or waiting list control in the treatment of hypertension with cognitive impairment and to explore its impact on microcirculation through hemodynamic and microcirculatory indices. The results of this trial will contribute to clarifying the microcirculatory mechanisms of electroacupuncture in the treatment of hypertension with cognitive impairment, providing a solid foundation for further research on electroacupuncture therapy.

**Trial Registration:**

Chinese Clinical Trial Registry ChiCTR2400083501; https://www.chictr.org.cn/showproj.html?proj=220722

**International Registered Report Identifier (IRRID):**

DERR1-10.2196/70876

## Introduction

### Background

Mild cognitive impairment (MCI) represents a transitional stage between normal cognitive function and dementia. In China alone, the incidence rate of MCI ranges from 9.7% to 23.3% [1], and the annual conversion rate of MCI to dementia is estimated to be 5% to 20% [2]. Hypertension is an independent and significant contributor to cognitive impairment; it increases the risk of MCI by 1.62 times. From 2007 to 2011, the prevalence of hypertension with MCI (HTMCI) was 16.5% [3]; meanwhile, a meta-analysis published in 2023 showed that the overall prevalence of HTMCI in China was 37.6% [4]. Evidence suggests that hypertension can increase the risk of cognitive-related diseases, such as Alzheimer disease (AD) and vascular dementia [5]. A meta-analysis [4] published in 2021 revealed that the combination of high blood pressure and MCI is associated with a global prevalence of up to 30%. A *Lancet* study reported that over the past 30 years, the number of adults aged between 30 and 79 years with high blood pressure has risen from 650 million to 1.28 billion [6]. As the prevalence of hypertension continues to rise, the number of patients experiencing both hypertension and cognitive impairment is expected to increase.

There are established pathways from hypertension to cognitive impairment, which include atherosclerosis and arteriolar sclerosis [7]. Cerebral hypoperfusion and reduced neurovascular coupling can result in brain dysfunction by depriving energy-demanding areas of oxygen and glucose, essential for cognitive processes [8]. Hypertensive amyloid production and deposition might also contribute by promoting the pathogenesis of cognitive impairment [9]. Hypertension is widely recognized as an important risk factor for cognitive impairment. However, cognitive impairment can lead to limitations in daily behavior and activities [10], subsequently affecting the drug management and nursing routines of patients with hypertension, resulting in a vicious cycle [11]. Therefore, determining ways to prevent or delay the progression of hypertension accompanied by MCI represents an urgent clinical challenge.

Microcirculation is the comorbidity pathologic basis of hypertension and cognitive dysfunction. Microcirculatory dysfunction is closely related to the occurrence and development of cognitive impairment. Studies have shown that microvascular endothelial cell abnormalities and cerebral blood flow regulation disorders can lead to local tissue hypoxia, changes in blood-brain barrier permeability, and decreased metabolic waste removal efficiency, which in turn accelerates β-amyloid deposition and tau protein hyperphosphorylation through mechanisms such as neurovascular unit disorders, enhanced oxidative stress, and neuroinflammatory activation, eventually leading to neuronal damage and decreased synaptic plasticity. So, improving microcirculation (microcirculation disturbance [MD]) is a key link in the process of prevention and cure of HTMCI, mainly reflected in the occurrence and development of hypertension [12,13]. MD-based cerebral blood flow regulation disorder and cerebral hypoperfusion are closely related to cognitive function impairment [13]; MD is the common pathophysiological basis of hypertension and cognitive impairment: they interact and influence each other through microvascular thinning degree, hemodynamics, oxidative stress level, endothelial cell function, etc [14-16].

In recent years, numerous studies have demonstrated that acupuncture exhibits significant antihypertensive effects on mild to moderate essential hypertension [17-20] and is increasingly recognized as beneficial in improving cognitive function [21-24]. However, reports on the effect of acupuncture on patients with both hypertension and cognitive impairment are lacking. Our team conducted a randomized controlled clinical trial of large-sample, multicenter acupuncture treatment of essential hypertension in the early stage and found that after 6 weeks of electroacupuncture treatment, the 24-hour average systolic blood pressure in the treatment group was significantly decreased (mean 7.2, SD 11.0 mm Hg) compared with the sham acupuncture group and the waiting treatment group, and the antihypertensive effect lasted for 6 weeks [25]. Another experiment to observe the effect of acupuncture on cognitive function in patients with poststroke cognitive impairment found that acupuncture significantly reduced the overall cognitive function of patients with poststroke cognitive impairment compared with the sham acupuncture group and the waiting treatment group and had a certain lasting effect and also reduced the incidence of dementia [26].

### Objectives

On the basis of the theory of MD and our previous research, this study will conduct randomized controlled experiments to explore the effect of electroacupuncture on improving cerebral microcirculation in improving cognitive function.

## Methods

### Trial Design

This is a multicenter, open-label, waiting list control randomized controlled trial. A total of 252 eligible participants will be randomly assigned in a 1:1:1 ratio to the electroacupuncture group, the sham electroacupuncture (SEA) group, and the waiting list group. The assessments of clinical outcomes will be performed at baseline, week 12, and week 24. Acupuncture treatment was administered once every other day, 3 times per week, for 12 weeks, followed by a 12-week follow-up. The flowchart and study design schedule are shown in Figures 1 and 2, respectively.

**Figure 1 figure1:**
[figure not shown]
Flowchart. HTMCI: hypertension with mild cognitive impairment; SEA: sham electroacupuncture.

**Figure 2 figure2:**
[figure not shown]
Location of acupoints and nonacupoints. Baihui: GV20; Fenglong: ST40; NA: nonacupoint; Neiguan: PC6; Shenting: GV24; Taichong: LR3; Zusanli: ST36.

### Ethical Considerations

The protocol has been approved by the institutional review board of the First Affiliated Hospital of Tianjin University of traditional Chinese medicine (TCM; TYLL2023{6}051). All patients provided their written informed consent to participate in the study and authorized the publication of their data. This study was registered on April 26, 2024, with the Chinese Clinical Trial Registry (ChiCTR2400083501). Every participant will be informed of detailed information about the study before signing informed consent. The results of this trial will be published in a peer-reviewed journal. Patients and the public were not involved in the design, or conduct, or reporting, or dissemination plans of this research.

### Participants and Recruitment

We will recruit participants in the outpatient departments of 3 hospitals, including the First Teaching Hospital of Tianjin University of TCM, the TCM hospital of Sichuan Province and Hospital of Chengdu University of TCM, the Affiliated Sichuan Provincial Rehabilitation Hospital of Chengdu University of TCM, and Tianjin Medical University General Hospital. Patients with HTMCI and healthy participants who are interested and whose initial screening meets our recruitment needs will be fully informed of the entire study procedure, benefits, and risks. Clinical trial communicators will fully explain the trial to patients before the trial begins to ensure that all the patients participate voluntarily and sign an informed consent form.

### Inclusion and Exclusion Criteria

The inclusion and exclusion criteria are presented in Textbox 1 [27-29].

Inclusion and exclusion criteria.
**Inclusion criteria**
Meet the diagnostic criteria of primary hypertension [27]Meet the diagnostic criteria of mild cognitive impairment [28]Mini-Mental State Examination ≥21 points and <27 pointsMontreal Cognitive Assessment Scale ≥18 points and <26 pointsActivity of daily living scale <22 points, and no more than 1 item in the single score may be ≥3 pointsAged between 40 and 75 yearsPrimary school education (6 years) or above and able to correctly understand and complete the scaleNo acupuncture treatment has been received within 3 monthsVoluntarily cooperate and sign informed consent
**Exclusion criteria**
Undergone treatments potentially interfering with cognitive functions, such as the use of cognition-impacting medications (eg, donepezil, memantine, and rivastigmine) [29]With neurological or chronic conditions, including systemic diseases (eg, anemia, tumors, and metabolic disorders) that could impair cognitive functionsPresence of infection or focal injury, as indicated by brain magnetic resonance imaging, multiple infarcts, or cerebral white matter lesions in critical memory areas (Fazekas Rating >3)With secondary hypertension, refractory hypertension, or hypertension accompanied by clinical syndromes and target organ damageWith aphasia, hearing impairment, muscle strength functional impairment below grade 3, severe visual impairment, or myopia exceeding 300, rendering them unable to cooperate with the testWith coexisting diabetes, hyperlipidemia, or a BMI <18.5 or ≥28Who is considered by the researcher to be unsuitable for this study

### Randomization and Blinding

A total of 252 eligible patients will be randomly allocated to the acupuncture group, the sham acupuncture group, and the waiting list group at a 1:1:1 ratio. An independent professional statistician, uninvolved in the trial’s implementation or subsequent statistical analysis, will generate the randomization sequence using SPSS (IBM Corp) software. Both the outcome assessor and the statistician will remain blinded to group assignments. Group assignments will be disclosed only after the completion of the statistical analysis.

### Interventions

All the groups receive standard treatment, including controlling blood pressure, blood glucose, blood lipid, and symptomatic treatment.

In this trial, 0.25×40 mm needles manufactured by HUATO, Suzhou, China, and the SDZ-III electroacupuncture apparatus by Suzhou Medical Appliance, Jiangsu, China, will be used. Interventions in all groups will be practiced by registered practitioners of TCM with at least 5 years of clinical experience in acupuncture. Acupuncturists will be trained in the study protocol and standardized acupuncture manipulations before study initiation.

### Electroacupuncture Group

Participants in the electroacupuncture group will receive electroacupuncture at Baihui (GV20), Shenting (GV24), Neiguan (PC6), Zusanli (ST36), Fenglong (ST40), and Taichong (LR3). Acupoints PC6, ST36, ST40, and LR3 will be applied bilaterally. All acupoints will be punctured to standardized needling depths and manipulated through lifting, thrusting, or twisting to induce the Deqi sensation. Three paired alligator clips from the electroacupuncture apparatus will be attached to GV20 and GV24, and to the homolateral ST36 and ST40, with a disperse-dense frequency (2/15 Hz) and a patient-tolerable current intensity. The precise locations and manipulations of these acupoints are depicted in Table 1 and Figure 2. This treatment will be administered over a period of 12 weeks, with sessions occurring once daily, 3 times per week.

**Table 1 table1:** Locations and manipulations of acupoints in the electroacupuncture group.

Acupoints	Location	Manipulation
Baihui (GV20)	On the midline of the head, 5 cm directly above the midline of the head, approximately on the midpoint of the line connecting the apexes of both ears.	Horizontal insertion with a depth of 1 cm is applied with a small-amplitude, high-frequency twisting technique of the reinforcing method for 1 min.
Shenting (GV24)	On the midline of the head, 0.5 cm directly above the midline of the head.	Horizontal insertion with a depth of 0.5-0.8 cm is applied with a small-amplitude, high-frequency twisting technique of the reinforcing method for 1 min.
Neiguan (PC6)	On the forearm, 2 cm above the transverse crease of the wrist, between the tendons of musculus palmaris longus and musculus flexor radialis.	Vertical insertion with a depth of 1.0-1.5 cm is applied with the twisting, lifting, and thrusting technique of the reducing method for 1 min.
Zusanli (ST36)	On the outer side of the calf, 3 cm directly below Dubi, and 1 finger-breadth lateral to the anterior border of the tibia.	Vertical insertion with a depth of 0.7-1.0 cm is applied with the twisting of 360°, with a frequency of 120-160 revolutions per minute of the mild reinforcing-reducing method for 1 min.
Fenglong (ST40)	One finger-breadth lateral to Tiaokou and at the midpoint of the line joining Dubi and the tip of the external malleolus.	Vertical insertion with a depth of 1.0-1.5 cm is applied with the twisting, lifting, and thrusting technique of the reducing method for 1 min.
Taichong (LR3)	On the dorsum of the foot, in the depression distal to the junction of the first and second metatarsal bones.	Vertical insertion with a depth of 1.0-1.5 cm is applied with the twisting, lifting, and thrusting technique of the reducing method for 1 min.

### The SEA Group

In the SEA group, 9 nonacupoints will be selected, with their locations detailed in Table 2 and Figure 2. The selection of nonacupoints in the SEA group involves choosing points situated on nonmeridians yet proximal to the acupoints selected in the electroacupuncture group, a common approach in sham acupuncture design [30]. A shallow needling technique (approximately 5 mm depth) will be used at these nonacupoints, eschewing both reinforcing-reducing techniques and the elicitation of the *Deqi* sensation. The SEA device will be connected, with its connecting wires internally disconnected. The number and frequency of treatments will mirror those of the electroacupuncture group.

**Table 2 table2:** Location of nonacupoints in the sham electroacupuncture group.

Nonacupoint	Location
Nonacupoint 1	At the midpoint of the line connecting the Fengchi acupoint (GB20) and the Anmian acupoint (Extra).
Nonacupoint 2	At the midpoint of the line connecting the Shenting acupoint (GV24) and Yintang acupoint (EX-HN 3).
Nonacupoint 3	On the palmar side of the forearm, on a level with Neiguan (PC6) and 1 cm radialis to it (between the Pericardium Meridian of Hand-Jueyin and the Lung Meridian of Hand-Taiyin).
Nonacupoint 4	In the middle of the Yanglingquan acupoint (GB34) and Zusanli acupoint (ST36; between the gallbladder and bladder meridian).
Nonacupoint 5	In the middle of the Fenglong acupoint (ST40) and the Zusanli acupoint (ST36; between the gallbladder and bladder meridian).
Nonacupoint 6	At the midpoint of the dorsum of the foot; the 3rd and 4th metatarsal bones join the anterior depression.

### Waiting List Group

No acupuncture treatment will be given in the waiting list group for the first 12 weeks. Participants will be required to complete the assessments at the corresponding time points. Considering the ethical requirements, compensatory treatment will be given after 12 weeks of following up.

The specific flowchart is shown in Figure 1.

### Outcomes

#### Baseline Comparability

We first confirmed the comparability of the baseline by independent 2-tailed *t* test for continuous variables and chi-square tests for categorical variables, all *P>*.05.

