### Statistical Analysis

Statistical analysis was performed using SPSS (version 27.0) software. All patients who completed the randomization and received the overall course of treatment were included in the efficacy analysis to ensure the integrity and comparability of the data. For different types of data, the following statistical methods will be used for analysis:

Data types and test methods: ×2 test is used for count data, and Shapiro-Wilk and Levene test are used for measurement data to analyze the independence, normality, and homogeneity of variance of data.Comparison between groups: for normal distribution and homogeneity of variance, 1-way ANOVA with completely random design was used for comparison between groups. If the variance is not uniform, the Kruskal-Wallis rank sum test of the single-factor nonparametric method of completely random design is used for comparison between groups. For the measurement data conforming to the skewed distribution, the Kruskal-Wallis rank sum test of the single-factor nonparametric method of completely random design was used for comparison between groups.Hypothesis testing and significance level: The count data are expressed as a ratio (%) using the chi-square test or Fisher exact test. The 2-sided test method was used uniformly, and the test statistics and corresponding *P* values were recorded. *P*<.05 was used as a criterion for judging significant statistical significance.

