## Results

The study protocol has been approved by the institutional review board of the First Affiliated Hospital of Tianjin University of TCM. This study was registered on April 26, 2024, with the Chinese Clinical Trial Registry. Data collection began in May 2024 and ended in April 2025. Currently, data from this trial are in the collection phase, and no data analysis has been performed. As of January 1, 2025, we have collected data from 65 patients. The results of this trial are expected to be submitted for publication in July 2026.

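### A baseline test result is reported although no analysis is said to have been done, and the fixed analysis of MoCA change leaves out the baseline MoCA covariate that is already collected

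*Protocol article*

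**What the plan says.** - **Baseline Comparability (under Outcomes):** "We first confirmed the comparability of the baseline by independent 2-tailed" t tests for continuous variables and "chi-square tests for categorical variables, all *P>*.05".
- **Results, and the same statement in the Abstract:** "Currently, data from this trial are in the collection phase, and no data analysis has been performed".
- **Abstract, Methods:** "The primary outcome will be the changes in overall cognitive function, as measured by the Montreal Cognitive Assessment". There are three arms, allocated 1:1:1.
- **Outcome Measures:** primary and secondary outcomes are measured at baseline, week 12 and week 24, so baseline MoCA is available.
- **Statistical Analysis:** for normal data with equal variances, "1-way ANOVA with completely random design was used for comparison between groups"; otherwise the "Kruskal-Wallis rank sum test of the single-factor nonparametric method of completely random design". Tests are two-sided at P<.05. No section names a baseline or other covariate.
- **Sample Size:** MoCA changes of 2.83 (SD 1.13), 1.97 (SD 1.38) and 0.48 (SD 1.65) for acupuncture, sham and waiting list; alpha 0.01, power 95%, 66 per group, 84 after 20% dropout.

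**The concern.** Two separate matters arise.

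First, a between-arm baseline test is a data analysis, and a statement about all its P values is a result. The article reports that result and also says there has been no analysis. The method does not fit either: an independent t test handles two groups, and the article does not say which pairs of the three arms were compared. Even a correctly chosen test would answer the wrong question. Under proper randomisation any baseline difference is due to chance, so a P value above .05 neither checks the randomisation nor shows that the arms are close enough on MoCA to leave the outcome comparison undisturbed.

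Second, the between-group analysis is written down as a one-factor comparison. This is a stated choice, not a detail left to an unseen analysis plan. Baseline MoCA is usually the strongest available predictor of later MoCA, and leaving it out of the model costs precision. It also leaves the estimate partly exposed to whatever imbalance chance produces, which matters most for electroacupuncture versus sham, where the planned difference is smallest.

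**Working it through.** **1. The statements side by side.** Baseline Comparability reports a completed set of tests with a uniform result. Results and the Abstract say no analysis has been performed. Either the tests were run, and the status statement is wrong, or they were not, and a result was written in advance. The documents do not say which.

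**2. What a clean set of baseline tests would tell us.** With k independent tests under perfect randomisation, the chance that all exceed .05 is 0.95^k: 0.95^10 = 0.60 and 0.95^20 = 0.36. The number of tests is not given and baseline measures are correlated, so these values are only illustrative.

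**3. The plan's own sample size, as a starting point.** Electroacupuncture versus sham: difference 2.83 − 1.97 = 0.86; pooled SD = √((1.13² + 1.38²)/2) = 1.261. At alpha 0.01 and 95% power, the normal approximation gives 68 per group one-sided (66 stated) and 77 two-sided. Dropout: 66/0.80 = 82.5, so 83 (84 stated); 3 × 84 = 252. The sidedness and the two alpha levels are separate issues. Here 66 per arm is only the base for comparison.

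**4. Power without a covariate.** Noncentrality = 0.86/(1.261 × √(2/66)) = 3.92 on 130 degrees of freedom. Exact noncentral t, two-sided:
- alpha 0.01 (critical t 2.61): 90.2%
- alpha 0.05 (critical t 1.98): 97.3%

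**5. Power with ANCOVA.** Let r be the correlation of baseline with week-12 MoCA, which the documents do not give. With equal SDs at the two times, the variance ratio of ANCOVA to change score is (1 − r²)/(2(1 − r)) = (1 + r)/2. The noncentrality becomes 3.92/√ratio.

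| Assumed r | Variance ratio | Power, alpha 0.01 | Power, alpha 0.05 |
|---|---|---|---|
| none (change score) | 1 | 90.2% | 97.3% |
| 0.8 | 0.90 | 93.3% | 98.4% |
| 0.4 | 0.70 | 98.0% | 99.6% |

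**6. If the SDs differ.** Entry restricts baseline MoCA to 18-25, so the follow-up SD may be the larger one. With k = follow-up SD/baseline SD, the ratio is k²(1 − r²)/(1 + k² − 2rk). At an assumed k = 1.25:
- r = 0.4: 1.5625 × 0.84/1.5625 = 0.84, a 16% reduction
- r = 0.5: 1.5625 × 0.75/1.3125 = 0.89, an 11% reduction
- r = 0.8: 1.5625 × 0.36/0.5625 = 1.00, no reduction

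**7. Residual effect of imbalance.** Subtracting baseline leaves a (1 − r) share of an imbalance in the change-score contrast (equal SDs). Assume a baseline MoCA SD of 1.5 to 2.5. At 66 per arm, the largest difference that is still non-significant is about 1.96 × SD × √(2/66), which is 0.51 to 0.85 points. For r of 0.8 to 0.5 the shift runs from 0.2 × 0.51 = 0.10 to 0.5 × 0.85 = 0.43 points, against a planned 0.86. A baseline test with P>.05 would not flag this; ANCOVA would adjust for it.

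**The case against.** The other side has good arguments, and several of them stand.

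- **A breach of blinding might be inferred**, since the article says "Group assignments will be disclosed only after the completion of the statistical analysis". The documents do not support that. Baseline can be compared across masked arm codes without disclosing assignments. The conflict shown is only with the statement that no analysis has been done.
- **The past tense may be loose drafting.** Statistical Analysis also uses it for planned work. That is fair, but the sentence gives an outcome of the tests, so it needs correcting on any reading.
- **A reader might infer that the tests serve in place of adjustment.** Nowhere does the article say that the baseline tests justify omitting covariates or steer the analysis.
- **A reader might take the analysis to ignore baseline altogether.** It does not. The outcome is change in MoCA, so baseline is already subtracted and only a residual share of an imbalance remains. One-way ANOVA on change is unbiased under randomisation. ANCOVA is a gain in efficiency and in protection against chance imbalance, not the repair of an invalid test.
- **The power gain looks best at alpha 0.01.** At the stated analysis level of 0.05 it is one to two percentage points on a comparison already above 95%. The 10-30% reduction in variance also depends on equal SDs.
- **Nothing requires a hospital term.** Randomization and Blinding describes no stratification by site, so leaving one out contradicts nothing.

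**Conclusion.** The point holds in two parts of different weight.

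The reporting conflict is certain from the text. The reported baseline result and the statement that no analysis has been performed are incompatible, the t test named does not fit three arms, and non-significance is not evidence of balance.

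The covariate-free comparison is valid but inefficient, and ANCOVA improves it at no cost. The size of that gain rests on assumptions about r and the SDs that the documents cannot settle. It is useful at alpha 0.01, small at 0.05, and could vanish if the follow-up SD is 1.25 times the baseline SD and r is 0.8. Under the equal-SD assumption, the residual shift from an undetected baseline imbalance could be about 0.1 to 0.4 points. The planned sample size is not wrong on account of this point.

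**What to change.** - Delete the baseline significance tests and the statement of their result. Present baseline characteristics by arm descriptively. If tests have in fact been run, correct the statement on analysis status and say when, and on what arm labels, they were done.
- Make the primary analysis an ANCOVA of week-12 MoCA with arm and baseline MoCA as terms, in place of the one-way ANOVA or Kruskal-Wallis choice. With baseline in the model, the arm contrast is the same whether the response is week-12 MoCA or change, so the primary outcome need not be redefined.
- Hospital may be added as a further covariate. This is optional.

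The cost is a change of wording. Baseline MoCA is already collected, and no extra patients or visits are needed. If, as the article states, nothing has been analysed, the change can still be prespecified and should be dated before any comparison by arm.
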